### Assessments

A series of standardised clinical assessments will be conducted at the enrolment visit (Visit 0) to assess inclusion and exclusion criteria (table 2), including:

Structured Clinical Interview for Diagnostic and Statistical Manual of Mental Disorders, Fifth Edition,^50^ to assess the presence of mental health and substance use disorders.A framework for clinical staging^18 51^ will be applied to assess illness severity and differentiate those in the earliest phases with non-specific clinical presentations (stages 1a ‘seeking help’) from those at greater-risk with more specific, subthreshold presentations (stage 1b ‘attenuated syndromes’) and those who have reached a threshold for a progressive or recurrent disorder meeting diagnostic criteria (stage 2, 3 or 4).SOFAS to record the clinician’s judgement of overall social and occupational function.A mental risk assessment to assess acute suicidal behaviour.

**Table 2 T2:** Overview of research assessments

Domain	Assessment	Administration	Time points (months)				
			0	3	6	12	24
Clinical diagnosis	Structured Clinical Interview to assess for DSM-5 Mental Health and Substance Use Disorders	Researcher administered	✓			✓	
Acute suicidal and aggressive behaviour (exclusion criteria)	CAARMS (7.3 and 5.4)	Researcher administered	✓				
Social and occupational functioning	SOFAS	Researcher administered	✓	✓	✓	✓	✓
Social and occupational functioning	PSP	Researcher administered	✓	✓	✓	✓	✓
Depressive symptoms	QIDS-C	Researcher administered	✓	✓	✓	✓	✓
Illness severity	Clinical staging	Researcher administered	✓	✓	✓	✓	✓
Quality of life	ReQoL-10	Self-report	✓	✓	✓	✓	✓
Self-harm/suicidal thoughts and behaviours	SIDAS/adaptation of the C-SSRS/B-NSS-AT	Self-report	✓	✓	✓	✓	✓
Alcohol and substance use	AUDIT-C: Alcohol use WHO-ASSIST: Alcohol and other substance use	Self-report	✓	✓	✓	✓	✓
Physical health	Height/weight/waist/BMI	Self-report	✓	✓	✓	✓	✓
Physical health	IPAQ (physical activity)	Self-report	✓	✓	✓	✓	✓
Physical health	Metabolic, inflammatory and standard clinical bloods	Researcher administered	✓		✓	✓	
Resource use	Resource Use Questionnaire	Self-report	✓	✓	✓	✓	✓

AUDIT-C, Alcohol Use Disorders Identification Test – Consumption; BMI, Body Mass Index; B-NSSI-AT, Brief Non-suicidal Self-injury Assessment Tool; CAARMS (7.3), Comprehensive Assessment of At-Risk Mental States – item 7.3; C-SSRS, Columbia-Suicide Severity Rating Scale; DSM-5, Diagnostic and Statistical Manual of Mental Disorders, fifth edition; IPAQ, International Physical Activity Questionnaire – short version; PSP, Personal and Social Performance Scale; QIDS-C, Quick Inventory of Depressive Symptomatology – Clinician-rated; ReQoL-10, Recovering Quality of Life Questionnaire (10-item version); SIDAS, Suicidal Ideation Attributes Scale; SOFAS, Social and Occupational Functioning Assessment Scale; WHO-ASSIST, WHO Alcohol, Smoking and Substance Involvement Screening Test (version 3.1).

As summarised in table 2, individuals who fulfil all inclusion and exclusion criteria will undergo additional clinician/researcher-administered baseline assessments evaluating depressive symptomatology, personal social performance and self-report questionnaires which will be provided to collect information regarding demographics, mental and physical health history, quality of life, self-harm, STBs, alcohol and substance use, and physical health. Furthermore, blood samples will be collected to assess metabolic, inflammatory, and standard blood markers.

While social and occupational functioning, illness severity, and depressive symptoms will be assessed at every subsequent visit (Visits 1–4), the structured clinical interview will only be repeated at the end of the active treatment phase (12 months after trial entry, Visit 3; and 24 months after trial entry, Visit 4). Self-report questionnaires will be provided at each visit during the active treatment phase (Visits 1–3). Blood samples will be collected at baseline, 6 months, and 12 months after trial entry (i.e., at visits 0, 2, and 3) to monitor changes in metabolic, inflammatory, and standard blood markers. Blood test results for young people in the intervention arm will be immediately relayed to treating clinicians, to provide more data to determine the appropriate treatment for the participant. For example, non-specific immunosuppressive therapies or innovative immune therapies could be the optimal treatment approach for young people with atypical major mood or psychotic disorders.

Resource use that will also be used to estimate costs will be measured using two main procedures:

Participants will be asked for access to administrative datasets including the Medicare Benefits Schedule and Pharmaceutical Benefits Schedule data for the duration of the study.The resource use questionnaire, used in multiple mental health economic evaluations, captures the broad range of health and welfare services used by participants and is complementary to any administrative data also included in the evaluation.^52 53^

Microcosting techniques will be used to assess the costs of the intervention. Standardised economic evaluation techniques, including incremental analysis of mean differences using generalised linear models and bootstrapping to determine confidence intervals, will also be conducted. Lifetime and population cost-effectiveness will be also determined using economic modelling techniques.

### Primary and secondary outcomes

Primary efficacy endpoint:

Changes in social and occupational function from baseline to 12 months, as assessed by the SOFAS.

Key secondary endpoints:

Change from baseline in self-harm, STBs (Brief Non-suicidal Self-injury Assessment Tool, B-NSSI-AT;^54^ Suicidal Ideation Attributes Scale, SIDAS;^55^ C-SSRS, Columbia-Suicide Severity Rating Scale).^56^Change from baseline in depressive symptoms (Quick Inventory of Depressive Symptomatology, QIDS).^57^Change from baseline in quality of life (Recovering Quality of Life Questionnaire, ReQoL).^58 59^Change from baseline in alcohol and substance use (WHO Alcohol, Smoking and Substance Involvement Screening Test, WHO-ASSIST;^60^ AUDIT-C, Alcohol Use Disorders Identification Test – Consumption).^61^Change from baseline in physical health (International Physical Activity Questionnaire – short version, IPAQ^62 63^; height, weight, waist).Change from baseline in metabolic, inflammatory and standard blood measures (metabolic and inflammatory markers, e.g., assessment of triglycerides, cholesterol, glucose, iron).Resource use as well as lifetime and population cost-effectiveness.Costs of the treatment packages based on detailed economic evaluation.

### Sample size calculation

This trial seeks to recruit 1500 young people, with 750 allocated to active 12-month intervention and 750 to standard clinical care. We anticipate an attrition rate of approximately 10%–20% over short-term follow-up (first 12 months) and up to 30% over the longer-term follow-up (at 24 months). Therefore, we would expect 1350 participants at 6 months follow-up (675 in each arm), 1200 participants at 12 months follow-up (600 in each arm) and 1050 participants at 2 years follow-up (525 in each arm). Assuming that we have at least 434 young people at the 2-year follow-up time point for the primary outcome analysis only, and conservatively assuming a small effect size difference of 0.2 in favour of those young people receiving the active intervention, with α=0.05, we have 95% power. For categorical secondary analyses with a small effect size of 0.2, α=0.05, and power=95%, the sample size at 2-year follow-up is 325 participants. There are also embedded subgroups for secondary analyses (e.g., by baseline suicidal behaviours, depressive subtype, alcohol or other substance misuse, and baseline SOFAS bands). For these subgroups, assuming that we have at least 195 young people at the 2-year follow-up time point for the primary outcome analysis only, and conservatively assuming a medium effect size difference of 0.3 in favour of those young people receiving the active intervention, with α=0.05, we have 95% power. For categorical secondary analyses with a medium effect size of 0.3, α=0.05, and power=95%, the sample size at 2-year follow-up is 144 participants.

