### Data analysis plan

The primary outcome will be analysed using a repeated-measure linear mixed model including all available SOFAS scores measured at months 0, 3, 6, 12, and 24. Fixed effects will include the randomised group, visit as a categorical variable, and the interaction between group and visit. The baseline SOFAS score will be included as a covariate alongside sex, age, and site (stratification variables). To account for correlations between repeated measures, a random patient intercept will be included. In case of convergence issues with the inclusion of the random effect, we will replace the random effect with a repeated effect assuming a compound symmetry covariance structure. This model will be used to derive the effect of the intervention at 12 months, expressed as the adjusted mean difference and its 95% confidence interval. The effect of the intervention at other timepoints will be estimated using a similar approach.

Secondary outcomes will be analysed using a similar approach. For binary outcomes, logistic regression (binomial distribution with logit link) will be used in place of linear regression. The effect of the intervention will be estimated as the odds ratio and 95% confidence intervals and converted to an absolute risk difference using the Hummel and Wiseman method.^64^ Given that linear mixed models use all data available and make valid inference under the assumption that data are missing at random, the primary analysis will not impute missing data; however, sensitivity analyses will be conducted to assess the robustness of the results under different assumptions about the missing data mechanism. A detailed statistical analysis plan including mock tables will be developed prior to unblinding and database lock.

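### The 95% power stated for 434 participants is not the power of the planned two-arm contrast at a standardised difference of 0.2, and it is set at 2 years although the primary endpoint is at 12 months

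*Protocol article*

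**What the plan says.** The Sample size calculation section of the protocol article plans 1500 participants, "with 750 allocated to active 12-month intervention and 750 to standard clinical care". On losses it says: "We anticipate an attrition rate of approximately 10%–20% over short-term follow-up (first 12 months) and up to 30% over the longer-term follow-up". From this it expects 600 per arm at 12 months and 525 per arm at 2 years.

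The power claim follows. Its condition is "Assuming that we have at least 434 young people at the 2-year follow-up time point for the primary outcome analysis only"; its effect is given by "conservatively assuming a small effect size difference of 0.2 in favour of those young people receiving the active intervention"; its result is "with α=0.05, we have 95% power". A parallel sentence for subgroups claims 95% power with at least 195 participants at 2 years and an effect size of 0.3. The section does not say whether 0.2 and 0.3 are standardised mean differences or another index, whether the test is one- or two-sided, whether 434 and 195 are totals or per arm, or whether any baseline correlation was assumed.

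Elsewhere the time point is fixed differently. Under Primary and secondary outcomes the primary endpoint is "Changes in social and occupational function from baseline to 12 months, as assessed by the SOFAS". Under Data analysis plan, the mixed model is put to this use: "This model will be used to derive the effect of the intervention at 12 months", reported as one adjusted mean difference between the arms.

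**The concern.** Two things do not fit.

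First, the power claim is labelled as the one for the primary outcome analysis, yet it refers to the 24-month visit. That is a year after active care ends, with a different expected sample and possibly a different effect. No power is stated for the 12-month contrast on which the trial will be judged.

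Second, a between-arm difference of 0.2 described as small reads naturally as 0.2 standard deviations. A two-arm trial needs roughly 1300 evaluable participants to detect that with 95% power, about three times 434.

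At stake is the accuracy of the only number that the article ties to power for its primary outcome. A reader who wants to know how much attrition the trial can tolerate would take from this sentence a margin that does not exist at the stated effect.

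**Working it through.** **Inputs from the protocol article.** N = 434 and effect 0.2; N = 195 and effect 0.3; α = 0.05; claimed power 95%; two arms, 1:1; 750 per arm randomised; attrition 10% to 20% by 12 months and up to 30% at 24 months. **Assumptions, not stated there:** the effect is a standardised mean difference d; the test is two-sided; no baseline adjustment. Alternatives are tried below.

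**Formula.** With n per arm and SD = 1, power ≈ Φ(d·√(n/2) − 1.96). The noncentral t agrees to within 0.2 percentage points where both were computed.

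**Attempt to reproduce 95% for the primary analysis, d = 0.2.**
- 434 in total, n = 217: 0.2 × √108.5 = 2.083; Φ(0.123) = 54.9% (noncentral t 54.7%). One-sided: 66.9%.
- 434 per arm: 0.2 × √217 = 2.946; Φ(0.986) = 83.8% (noncentral t 83.7%). One-sided: 90.3%.
- Needed for 95%: n = 2 × (1.960 + 1.645)² / 0.2² ≈ 650 per arm (651 by noncentral t). One-sided: 542.
- Smallest difference detectable with 95% power at 434 in total: 3.605 × √(2/217) = 0.346 SD.

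The 95% is not reproduced.

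**Subgroup figure, d = 0.3.**
- 195 in total, n = 97.5: 0.3 × √48.75 = 2.095; Φ(0.135) = 55.4%.
- 195 per arm: 84.2%.

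**Where the numbers probably come from (inference).** For an F test with 3 numerator degrees of freedom and noncentrality f²N, the smallest N with at least 95% power is exactly 434 at Cohen's f = 0.2 (95.04%) and exactly 195 at f = 0.3 (95.03%). At f = 0.2, 1, 2 and 4 degrees of freedom need 327, 390 and 470 instead. Two exact matches make coincidence unlikely, but the article states neither f nor 3 degrees of freedom. The planned contrast has 1 degree of freedom. For two equal arms d = 2f, so f = 0.2 is d = 0.4, twice the difference described. On that reading 434 in total gives the contrast 0.4 × √108.5 = 4.167; Φ(2.207) = 98.6%, again not 95%.

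**Effect of baseline adjustment.** The model adjusts for baseline SOFAS, which multiplies the variance by about 1 − ρ². The article gives no ρ, so a range is shown for d = 0.2, two-sided:

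| ρ | 434 in total | 434 per arm | 600 per arm |
|---|---|---|---|
| 0 | 54.9% | 83.8% | 93.4% |
| 0.3 | 58.9% | 87.0% | 95.3% |
| 0.5 | 67.2% | 92.5% | 97.9% |
| 0.7 | 83.1% | 98.5% | 99.8% |

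To reach 95%, 434 in total needs ρ of about 0.82, and 434 per arm about 0.58.

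**Power of the design as planned, d = 0.2, two-sided, unadjusted.**
- 12 months, 20% attrition: 750 × 0.8 = 600 per arm; 0.2 × √300 = 3.464; Φ(1.504) = 93.4% (noncentral t 93.3%).
- 12 months, 10% attrition: 750 × 0.9 = 675 per arm; 0.2 × √337.5 = 3.674; Φ(1.714) = 95.7%.
- 24 months, 30% attrition: 750 × 0.7 = 525 per arm; 0.2 × √262.5 = 3.240; Φ(1.280) = 90.0% (noncentral t 89.9%).

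**The case against.** The strongest reply is that nothing practical hangs on 434. It is given as a floor, straight after expected numbers of 1200 at 12 months and 1050 at 2 years, and the target of 1500 is fixed throughout the article. At those numbers unadjusted power at 12 months is 93% to 96%, so the claimed 95% lies inside the range that the trial's own attrition figures imply. Adjustment for baseline pushes it up: an assumed ρ of only 0.3 is enough at 600 per arm. This stands, and it limits the consequence to the correctness of the stated justification.

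It can also be said that the planned analysis is not an unadjusted t test and that the metric of 0.2 is not named. That stands in part. A reader might infer that no two-arm reading could reach 95%; that goes too far. Cohen's f = 0.2 gives 98.6% with 434 in total, and 434 per arm reaches 95% if ρ is about 0.58. But the article invokes neither f nor a correlation, and f = 0.2 would contradict its description of a small difference of 0.2 as a conservative assumption.

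On timing, sizing at the visit with the fewest participants is conservative on numbers, and month-24 scores enter the mixed model. Neither makes the 24-month contrast the primary one.

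Finally, this is not detail that may be left to a statistical analysis plan: it is a stated figure that does not follow from the stated inputs.

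**Conclusion.** The point holds as a correction of the stated calculation. The power claim for the primary analysis is set at 2 years, whereas endpoint and contrast are at 12 months; that is plain from the text. The claimed 95% is not the power of the planned contrast at a standardised difference of 0.2: it is about 55% with 434 in total and about 84% with 434 per arm. The subgroup claim fails in the same way, at about 55% for 195 in total. These values assume a two-sided 0.05 test, the d metric and no baseline adjustment. The F-test origin of 434 and 195 is an inference.

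A reader might conclude that the trial is underpowered, or that recruitment could stop near 434 with little better than even odds of detecting the target effect. The article supports neither. It contains no rule for stopping at 434, it plans for the full 1500, and at its own expected numbers the trial has about 93% to 96% unadjusted power at 12 months.

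**What to change.** Delete 434 and restate power for the two-arm contrast at 12 months. Name the effect metric, the sidedness, any assumed baseline correlation, and whether N is total or per arm. Suggested wording: *With 600 to 675 participants per arm at 12 months (20% to 10% attrition), power is 93% to 96% at two-sided alpha 0.05 for a standardised difference of 0.2, before baseline adjustment.* Give about 90% for 525 per arm at 24 months as supportive information.

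Correct the subgroup sentence in the same way: either state the power that 195 actually gives for the planned contrast at 0.3, or state the number needed. Unadjusted and two-sided, 95% power at d = 0.3 needs 2 × (1.960 + 1.645)² / 0.3² ≈ 289 per arm. If another test or index was intended for 434 and 195, say so and show how it relates to the planned contrast.

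The cost is a text amendment. It needs no extra participants and no change to the analysis. At the pessimistic end of attrition the stated power for the primary contrast falls from 95% to 93%.

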The differentiation of young people with ‘reasonable/good’ from ‘impaired/poor’ functioning at presentation is a key factor to be considered (alongside other clinical variables) to determine the need for highly personalised care with the appropriate type, intensity, sequence, and duration of multidisciplinary interventions. This approach aligns with optimal models of mental health care and should be a key component of youth mental health service provision.^18^ Yet, the evidence-base for health service models that guide personalised interventions for young people with mood disorders is sparse.^19–22^ Furthermore, it is not standard practice to use measurement-based care (MBC) for the monitoring of symptoms and functioning to drive continuous and personalised clinical decision-making.^23–27^ Highly personalised and MBC, which entails routine assessment of multidimensional outcomes and regular monitoring of an individual’s response to treatment, is a core component of the chronic care model and supports better-informed clinical decisions.^28–34^ These decisions may include the adjustment of treatment type and intensity. Despite good evidence for its effectiveness and its customary use in physical disease management,^31 32^ it remains largely absent from youth mental health care.^9 35^

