### Inclusion and exclusion criteria

Participation in this study will be offered to adolescents and young adults aged 15–25 years seeking help for psychological distress and classified as clinical stage 1a, 1b, or 2. The participants must have an initial Social and Occupational Functioning Assessment Scale (SOFAS) score of ≤70,^37^ indicating an impaired social and occupational functioning. Additional exclusion criteria includes acute suicidal or aggressive behaviour requiring alternative care or a depressive syndrome secondary to a primary medical condition. Young people who have a clinically evident intellectual disability (IQ<70 as per medical history review) will be excluded due to the likely difficulty in completing the assessments.

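### Baseline SOFAS is named as a subgroup factor only in bands, although the score is already in the model; a continuous group-by-score interaction would be a more efficient main analysis of this modifier

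*Protocol article*

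**What the plan says.** The Sample size calculation section states: "There are also embedded subgroups for secondary analyses (e.g., by baseline suicidal behaviours, depressive subtype, alcohol or other substance misuse, and baseline SOFAS bands". The sizing given there reads "For these subgroups, assuming that we have at least 195 young people at the 2-year follow-up time point for the primary outcome analysis only", with an effect size of 0.3 and 95% power. The section states no number of bands, no cut-points and no test of effect modification.

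The Data analysis plan uses the same variable as a score: "The baseline SOFAS score will be included as a covariate alongside sex, age, and site (stratification variables". The one interaction it lists is group by visit: "Fixed effects will include the randomised group, visit as a categorical variable, and the interaction between group and visit". It leaves detail to a later statistical analysis plan.

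Two other places bear on the point. Entry is capped under Inclusion and exclusion criteria: "The participants must have an initial Social and Occupational Functioning Assessment Scale (SOFAS) score of ≤70". The Introduction says that telling better from poorer functioning when a young person presents "is a key factor to be considered (alongside other clinical variables) to determine the need for highly personalised care".

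**The concern.** One variable takes two forms. It is a score where it adjusts the treatment comparison, and bands where it is to describe who benefits more or less. Bands treat participants one point apart on either side of a cut as different, and participants several points apart within a band as the same. The cap at 70 already shortens the range being split.

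At stake is the power of one secondary question, whether the benefit of HP&MBC varies with baseline functioning. The answer would also depend on cut-points that the article does not give. Missing cut-points or a missing interaction test would not be a finding in themselves, since an article commonly leaves these to the analysis plan. The point is the form that the text names, which an analysis plan following this wording would inherit.

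**Working it through.** **The plan's own figures.** The subgroup size of 195 and the whole-sample size of 434 reproduce as an F test with 3 numerator degrees of freedom, α = 0.05 and the effect size read as Cohen's f. The non-centralities are 195 × 0.3² = 17.55 and 434 × 0.2² = 17.36, and each gives power 0.950. The categorical figures of 325 and 144 reproduce as a 1-df chi-square with w = 0.2 and 0.3 (324.9 and 144.4). None of these depends on how baseline SOFAS is coded, so they neither support nor contradict the point.

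**Inputs for the loss from banding.** From the article: baseline SOFAS is at most 70. Assumed, because the article does not give them: whole-number scores; a normal distribution with mean 58–65 and SD 8–10 before truncation at 70; cut-points; and a treatment effect that changes linearly with the score.

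**Formulas.** For a linear modifier, the share of information kept is r = (between-band variance of the score) / (total variance of the score).
- A test on the continuous score with 80% power, two-sided α = 0.05, has non-centrality λ = (1.96 + 0.8416)² = 7.85. Banding reduces it to λr.
- With two bands, or a 1-df trend across bands scored by their means, power = Φ(√(λr) − 1.96).
- With three unordered bands, power comes from a non-central chi-square on 2 df with non-centrality λr.

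**Results over the assumed means and SDs.**

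| Bands | r | Loss | Power, 1 df | Power, 2 df |
|---|---|---|---|---|
| Two, cut at 60 | 0.56–0.68 | 32–44% | 56–63% | – |
| Three (≤50, 51–60, 61–70) | 0.78–0.84 | 16–22% | 70–73% | 59–63% |
| Two, cut at 50 | 0.29–0.61 | 39–71% | 33–59% | – |

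Worked example, two bands cut at 60, mean 58, SD 10: r = 0.562, λr = 7.85 × 0.562 = 4.41, √4.41 = 2.10, and Φ(2.10 − 1.96) = Φ(0.14) = 0.56.

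**Sensitivity to the assumptions.** For an untruncated normal baseline and equal-sized bands, the loss is 36%, 21%, 14% and 10% with two, three, four and five bands. For a uniform baseline it is 25%, 11%, 6% and 4%. The lowest loss examined is therefore about 4% (five bands, uniform) and the highest about 70% (two bands cut at 50; mean 65, SD 8). Moving the two-band cut from 60 to 50, with mean 65 and SD 8, changes r from 0.68 to 0.29. That shows how far the result can hang on the cut.

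**The case against.** The strongest reply is that the article fixes no analysis of this modifier. Bands are one item in a list of examples, in a section about sample size. The Data analysis plan specifies no subgroup analysis, and nothing excludes a continuous interaction alongside the bands. This stands. A reader might infer that a banded moderator analysis is settled, but the text supports only that bands are the one form named.

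A reader might also infer a definite loss of information about whom HP&MBC helps. That is not supported. The size rests on assumed inputs and on linear modification, and it concerns one example modifier. The three-band power also depends on the test: about 59–63% for an unordered 2-df test, but 70–73% for a trend.

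Nor does the Introduction rank baseline functioning as the most important modifier. It calls it a key factor alongside other clinical variables, and it speaks of functioning in categories, so bands fit the authors' clinical language. That is a good reason to report by band. It does not require the test to discard differences within bands.

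Finally, if the effect is stepped or non-monotone in SOFAS, a linear term is the wrong shape. This stands as a limit on the remedy.

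**Conclusion.** The point holds as a minor efficiency point about one secondary analysis. The article names bands for a variable that it already holds and models as a score. If the modifier is assessed through those bands, power is lost and the conclusion can shift with the cuts. Under the stated illustrative assumptions the loss is about 32–44% with two bands cut at 60 and about 16–22% with three 10-point bands. These are not figures for this trial, because the bands and the baseline distribution are not given.

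A reader might suppose that the primary comparison is weakened too. It is not: that model keeps the score as a covariate. The other named subgroups (suicidal behaviours, depressive subtype, substance misuse) are not touched either.

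**What to change.** In the statistical analysis plan, make the main analysis of this modifier a randomised group by continuous baseline SOFAS term for the 12-month effect. In the repeated-measures model, that means letting the product of group and score vary by visit, with its lower-order terms. Add a restricted cubic spline in baseline SOFAS as a check for non-linearity. Report the estimated 12-month difference with its 95% CI at a few pre-stated scores, for example 45, 55 and 65, with a figure across the observed range. Keep bands for display only, with cut-points stated in advance.

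The cost is one added model specification and one figure, with no new data. The drawback is that a linear term can be misspecified if modification is stepped. The spline addresses this at the price of extra degrees of freedom. The article says that the analysis plan will be written before unblinding and database lock, so the form can be set before results could influence it.

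### The subgroup power statement is wrong as written: 195 participants give about 55% power, not 95%, for a two-arm standardised difference of 0.3

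*Protocol article*

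**What the plan says.** The Sample size calculation section of the protocol article gives separate power statements for the whole sample and for subgroups. The subgroups named as examples are baseline suicidal behaviours, depressive subtype, alcohol or other substance misuse, and baseline SOFAS bands.

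For continuous outcomes within subgroups the inputs are:

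- size: "For these subgroups, assuming that we have at least 195 young people at the 2-year follow-up time point for the primary outcome analysis only"
- effect: "conservatively assuming a medium effect size difference of 0.3 in favour of those young people receiving the active intervention"
- error rates: "with α=0.05, we have 95% power"

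For categorical outcomes the section says "For categorical secondary analyses with a small effect size of 0.2, α=0.05, and power=95%, the sample size at 2-year follow-up is 325 participants" and, for subgroups, "For categorical secondary analyses with a medium effect size of 0.3, α=0.05, and power=95%, the sample size at 2-year follow-up is 144 participants".

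No test, effect-size metric or sidedness is given for any of these. The Abstract and the Study design and setting section describe two arms randomised 1:1. The Data analysis plan section estimates an adjusted mean difference between the arms for continuous outcomes, and an odds ratio converted to a risk difference for binary outcomes.

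**The concern.** In a two-arm trial analysed by a mean difference, an effect size expressed as a difference favouring one arm is naturally read as a standardised mean difference (Cohen's d). On that reading, 95% power at 0.3 from 195 people looks far too favourable.

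What is at stake is how the subgroup results are read. The section tells readers that a subgroup of about 195 has very high power for a 0.3 SD effect. If the true power is near one half, a non-significant result in such a subgroup says little about whether the effect is absent.

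**Working it through.** **Inputs.** From Sample size calculation: N = 195, effect 0.3, alpha 0.05, power 95%, and 1050 participants expected at 24 months. From the Abstract: two arms, 1:1. Assumed here because the protocol is silent: two-sided test, equal arms within the subgroup, no covariate adjustment. One-sided results are also shown.

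**1. Reproducing 195.** For an F test with Cohen's f, the noncentrality is λ = N·f². With 3 numerator df and f = 0.3:

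- N = 194: λ = 194 × 0.09 = 17.46, power 0.9492
- N = 195: λ = 195 × 0.09 = 17.55, power 0.9503

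So 195 is the smallest N that reaches 95%. The whole-sample figure of 434 in the same section comes out the same way with f = 0.2: N = 433 gives 0.9499 and N = 434 gives 0.9504. Two exact matches make coincidence unlikely. With two equal groups d = 2f, so f = 0.3 corresponds to d = 0.6, twice the stated difference. A two-arm contrast has 1 numerator df, and at f = 0.3 it would need 147, so 195 does not fit a two-arm comparison even in the f metric.

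**2. Power for the difference described.** For two arms of n each, the noncentrality is δ = d·√(n/2), and power comes from the noncentral t distribution with 2n − 2 df.

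| Reading of 195 | n per arm | δ | Two-sided power | One-sided power |
|---|---|---|---|---|
| Total | 97.5 | 0.3 × √48.75 = 2.095 | 0.549 | 0.671 |
| Per arm (390 in total) | 195 | 0.3 × √97.5 = 2.962 | 0.840 | 0.905 |

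Neither reading reaches 95%, one-sided or two-sided.

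**3. Size needed for 95%.** The normal approximation gives a total of 4(1.960 + 1.645)²/0.3² = 577.5, or 289 per arm. With the t distribution, 289 per arm gives 0.9495 and 290 per arm gives 0.9502, so 290 per arm, 580 in total. The one-sided normal approximation gives 241 per arm, 482 in total. Against the 1050 expected at 24 months, 580 is 580/1050 = 55%, so at most one category of any subgroup factor could reach it.

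**4. Effect of baseline adjustment.** A baseline correlation r multiplies the residual variance by 1 − r², so the effective difference becomes 0.3/√(1 − r²). The protocol gives no r; the values below are illustrative.

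| r | Effective d | Power, 195 in total | Power, 195 per arm |
|---|---|---|---|
| 0.5 | 0.346 | 0.67 | 0.93 |
| 0.6 | 0.375 | 0.74 | 0.96 |

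For 195 in total to reach 95%, 1 − r² must fall to 195/580 = 0.336, so r = √0.664 = 0.81.

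**5. The categorical figures.** For a 1-df chi-square test with Cohen's w, λ = N·w².

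- w = 0.2, N = 325: λ = 13.00, power 0.9501
- w = 0.3, N = 144: λ = 12.96, power 0.9495 (145 gives 0.9508)

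Both hold as stated, within rounding. With equal arms, w = 0.2 is for example 60% vs 40% (odds ratio 1.5/0.667 = 2.25), and w = 0.3 is for example 65% vs 35%.

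**The case against.** **The metric is not named, so 0.3 might have been meant as Cohen's f.** The 3-df F origin is indeed an inference from the numbers. But the sentence describes a difference in favour of one arm, and f is not such a difference. The stated power fails for the difference described, whatever its origin.

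**The planned model adjusts for baseline SOFAS and uses repeated measures, so unadjusted power is pessimistic.** This stands as a condition on the 55% and the 580. It does not rescue 195 as a total: at correlations of 0.5 to 0.6 power is still only 67% to 74%. Read as 195 per arm, a correlation of about 0.57 would suffice (√(1 − 390/580)), but the section says neither that 195 is per arm nor that any correlation was assumed.

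**The figure does not set the sample size.** True. Recruitment is fixed at 1500, and the subgroup analyses are secondary. This limits the consequence but does not make the statement correct.

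A reader might also go further in two ways that the protocol does not support:

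- *That 325 and 144 are wrong too.* Those sentences give an effect size for categorical analyses and describe no difference between arms. In w, a standard metric for a two-arm binary comparison, the stated power is right. Nothing in the protocol requires the categorical effect to match a 0.2 or 0.3 SD mean difference, so a recalculation on that basis would test an assumption the plan does not make.
- *That the plan wrongly relies on within-subgroup tests instead of treatment-by-subgroup interactions.* The section specifies no subgroup test and claims no differential effect. How subgroups are tested and labelled ordinarily belongs in the statistical analysis plan, which the article says will be written and which is not shown.

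**Conclusion.** The point holds for the subgroup figure of 195 only. For a two-arm difference of 0.3 SD at two-sided alpha 0.05 without covariate adjustment, 195 in total gives about 55% power and 195 per arm about 84%, against the stated 95%. About 580 analysed participants are needed, roughly three times the stated number (580/195 = 2.97).

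This rests on reading 0.3 as a standardised mean difference, which the wording supports, and on equal arms within the subgroup. The explanation through a 3-df F test with f = 0.3 is a well-supported inference, and the verdict does not depend on it. The statement should be corrected, but it concerns secondary analyses and does not affect recruitment.

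**What to change.** Replace the continuous subgroup statement in Sample size calculation with a correct one. Either say that about 580 analysed participants (290 per arm) are needed for 95% power at a standardised difference of 0.3, or keep 195 and say that it gives about 55%. Name the test, the metric and the sidedness, say whether the number is a total or per arm, and state any baseline correlation relied on.

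Leave 325 and 144 as they are. At most, add that they are 1-df chi-square sizes with w = 0.2 and w = 0.3, with example proportions such as 60% vs 40% and 65% vs 35%.

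The cost is a change of text and a less favourable published figure. Recruitment and data collection do not change.
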